#### Descriptive statistics

Categorical variables will be summarised using frequency and percentage. Continuous variables will be summarised using mean, SD and/or SE and range; or median, IQR and range as appropriate. Event data will be presented as point estimates with associated 95% CI presuming an underlying Poisson, negative binomial or zero-inflated distribution as appropriate.

#### Inferential statistics

Comparisons of event proportions between the prospective cohort and historical controls will be conducted using a χ^2^ test, Fisher’s exact test or linear mixed modelling as appropriate. Associations between participant characteristics and study outcomes will be explored using univariable and multivariable logistic, Poisson and/or negative binomial regression and/or linear mixed modelling as indicated. Multivariable models will be assessed for collinearity and interactions between explanatory covariates. Adjustment for clinic effects will be conducted by including the clinic identifier as a random effect in the aforementioned models. The final selection of test or model type will be confirmed on initial review of the collected data, with consideration given to the number of available events for each outcome. For all analyses, p<0.05 will be considered significant. All analyses will be undertaken using R statistical computing software, V.4.4.2^46^ and/or Stata, statistical software, V.18.^47^

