Delivered by telehealth, the PCMed Service is intended for women at substantially increased risk of a first breast cancer who are interested in considering taking medications to reduce their risk. Referrals are accepted from clinicians from the PMCC and surrounding services who routinely see women at increased risk of breast cancer. These referring clinics will henceforth be referred to as ‘catchment clinics’; they include Late Effects, Breast Surgical and Familial Cancer Clinics at PMCC and the Familial Cancer Clinic at the Royal Melbourne Hospital. Referrals are also accepted from clinics external to the catchment clinics and from PCPs. Women who attend the PCMed Service are referred to as clients.

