### Statistical considerations and analyses

#### Sample size considerations

The prospective sample size required for the primary outcome will depend on the uptake of RRMeds in the historical cohort. We will identify 100 consecutive historical controls. Based on Australian data,^25^ we expect the uptake of RRMeds in the historical cohort to be 2%. Based on the clinical judgement of the investigators, we consider an increase from a baseline of 2%, prior to the commencement of the PCMed Service, to 20% after its implementation to be clinically significant enough to warrant implementation of this complex intervention. A prospective sample size of 57 clients who attend the PCMed Service from catchment clinics will be required to provide 80% power to detect a minimum change from 2% to 20% at a 5% significance level. To account for a possible 10% loss to follow-up, we will recruit a sample of 63 consenting clients from catchment clinics as they attend the PCMed Service. If the uptake of RRMeds (in the historical cohort) is substantially different from 2%, the prospective sample size will be adjusted.

Recruitment to the Service and the study commenced on 14 November 2023. To date, 100 women (historical controls) have been recruited to the retrospective component of the study and 278 women to the prospective component of the study. Thirty-five of the prospectively recruited women are eligible for the analysis of the primary outcome; the remainder are eligible for other outcome analyses.

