#### Analysis of the primary outcome

##### Effectiveness of the PCMed Service intervention

The proportion of women who start RRMeds within 12 months of a catchment clinic consultation will be summarised preimplementation and postimplementation of the PCMed Service using descriptive statistics. Event proportions will be compared using a χ^2^, Fisher’s exact test or linear mixed modelling as indicated. Differences in the distribution of confounders between the historical and prospective cohorts will be managed using univariable and multivariable logistic, Poisson and/or negative binomial regression and/or linear mixed modelling as indicated.

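### Clinic adjustment by a random effect over about four clinics and 13 events is likely to under-adjust, and a linear mixed model does not suit the yes/no primary outcome

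*Protocol article*

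**What the plan says.** The primary outcome is one yes/no value per woman: "The proportion of women who start RRMeds within 12 months of a catchment clinic consultation" (Analysis of the primary outcome).

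- **Clinic.** Inferential statistics: "Adjustment for clinic effects will be conducted by including the clinic identifier as a random effect in the aforementioned models". The sentence carries no qualifier and applies to whichever model is chosen.
- **Clinics named.** Intervention section: "they include Late Effects, Breast Surgical and Familial Cancer Clinics at PMCC and the Familial Cancer Clinic at the Royal Melbourne Hospital". Read as a list, that is four.
- **Comparison and adjustment.** The two proportions may be compared by χ² test, Fisher's exact test or linear mixed modelling. For adjustment, "Differences in the distribution of confounders between the historical and prospective cohorts will be managed using univariable and multivariable logistic, Poisson and/or negative binomial regression", with linear mixed modelling again an option.
- **Intervals.** Descriptive statistics gives 95% CIs for event data "presuming an underlying Poisson, negative binomial or zero-inflated distribution as appropriate". The binomial is not listed.
- **Choice of model.** "The final selection of test or model type will be confirmed on initial review of the collected data", taking into account how many events each outcome has.
- **Size.** "We will identify 100 consecutive historical controls", and "we expect the uptake of RRMeds in the historical cohort to be 2" per cent, against 20% in 57 clients (Sample size considerations).

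**The concern.** The comparison is non-randomised. Under Analysis sets, the primary set sets women who chose to attend the Service against consecutive historical controls from the same clinics. Clinic mix may differ between the two groups. Clinics may also differ in practice: the outcome section notes that the familial cancer clinics routinely apply a risk model, while the others did not do so consistently. Clinic adjustment is therefore one of the main protections of the primary result.

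A random intercept adjusts only as far as its variance is estimated to be above zero. Four clinics and about 13 events carry little information on that variance. If it is estimated as zero, a model reported as clinic-adjusted is in effect unadjusted.

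Separately, a linear mixed model assumes one residual variance for both cohorts. A binary outcome at 2% and 20% has very unequal variances, so the interval for the difference in uptake is at risk.

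**Working it through.** **Inputs from the protocol.** Controls 100 at 2%; clients 57 at 20%; four named clinics. The stated 57 is reproduced by the two-sided, continuity-corrected formula for 2% v 20%, 80% power, 5% level and equal groups (57 per group; 47 without the correction). That figure is not in dispute here.

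**1. Expected events.** 100 × 0.02 = 2 and 57 × 0.20 = 11.4, about 13 in all. P(no control event) = 0.98^100 = 0.133. In that case unpenalised logistic regression has no finite cohort estimate.

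**2. Does the clinic variance survive?** Random-intercept logistic model, four clinics, 100 v 57 women. Share of runs with the variance at about zero:

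| True between-clinic SD (logit) | Variance estimated as about zero |
|---|---|
| 0 | 79% |
| 0.5 | 52% and 53% (two separate simulations) |
| 1.0 | 29% |

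**3. Consequence under no true effect.** Clinic rates and mixes are assumptions; the protocol gives none.

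- *Scenario A:* clinic uptake 6/2/0.5/0.5%, 25 controls per clinic, attenders 30/17/5/5. Expected control events are 25 × (0.06 + 0.02 + 0.005 + 0.005) = 2.25 in 100. Expected client events are 30 × 0.06 + 17 × 0.02 + 5 × 0.005 + 5 × 0.005 = 2.19 in 57, or 3.8%. Clinic mix alone thus separates 2.25% from 3.8%.
- *Scenario B:* clinic log-odds offsets −1, −0.3, 0.3, 1; control mix 40/30/20/10%, reversed in clients; 500 runs. Random-intercept results are among runs with a finite estimate.

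| Scenario | Random intercept: rejection; median log-OR | Clinic as stratum or fixed effect: rejection; median log-OR |
|---|---|---|
| A | 10.4% to 12.9% over repeated simulations; +0.55 | CMH 2.8% to 4.1%; Firth 2.3%, about 0 |
| B, control rate 5% | 6.6%; +0.34 | Firth 2.6%; −0.03 |
| B, control rate 2% | 3.1%; +0.57 | Firth 1.0%; +0.13 |

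In the last row, 23% of runs gave no finite random-intercept estimate. In scenario B with a true 2% v 20% effect (log-OR 2.51), the random intercept had median 2.85 and Firth 2.41, with Firth coverage 95.6%. With the same clinic mix in both cohorts, the random intercept was close to the truth (median 2.45).

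**4. Linear model for 2% v 20%**, taking 2/100 and 11/57 (p₁ = 0.02, p₂ = 0.193).

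- Unequal-variance SE = √(0.02 × 0.98/100 + 0.193 × 0.807/57) = 0.0541.
- Common variance s² = (100 × 0.02 × 0.98 + 57 × 0.193 × 0.807)/155 = 0.0699, so SE = √(0.0699 × (1/100 + 1/57)) = 0.0439.
- Ratio 0.0439/0.0541 = 0.81, that is, 19% too small.

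Enumerating all outcomes at true rates of 2% and 20%, the nominal 95% interval covers 87.9% with the common-variance SE and 93.6% with the unequal-variance SE. The larger group has the smaller variance, so pooling understates the error.

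**5. Poisson intervals for a proportion.** 2/100: Poisson 0.24% to 7.2%, exact binomial 0.24% to 7.0%. 11/57: 9.6% to 34.5% against 10.0% to 31.9%. Unadjusted Poisson gives a log risk ratio SE of 0.769 against 0.751 (+2.4%) and coverage of 97.1%. At these rates the error is small and on the wide side.

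**The case against.** - **The error rates rest on invented scenarios.** This stands. The protocol gives no clinic-level rates or mix, and false-positive inflation is not universal: scenario B at a 2% control rate rejected only 3.1%. Part of the scenario A excess comes from a likelihood-ratio test on about four events. With uptake of 2.25% in every clinic that test already rejected 7.0%, and in one repeat 5.6 of its 10.4 percentage points came from runs with no control event. Unadjusted Fisher, which the plan lists, rejected 5.1% in scenario A. The variance collapse and the upward bias remain.
- **A reader might infer that the random-effect model gives wrong error bars.** The checks do not support that: its 95% coverage was 93% to 99.5%. Its fault is under-adjustment, and no finite estimate when controls have no events.
- **A reader might infer that Poisson, negative binomial and zero-inflated models are all prescribed for the primary outcome.** They are not. The lists serve every outcome, including true counts such as consultations and hotline calls, and say as appropriate or as indicated. Zero-inflated appears only under Descriptive statistics. Logistic regression and Fisher's test are also listed.
- **The choice will consider event counts, and the final test belongs in the SAP.** Largely accepted: not naming one test or a covariate list in an article is no finding. But the clinic rule is stated here without qualification, and the linear mixed model is offered for the primary comparison itself.
- **Four clinics is a reading.** The list is introduced by a word that allows more, so about four is the fair statement.

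**Conclusion.** The point holds in limited form, as a cheap improvement; within it, the linear mixed model option is wrong as written.

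- **Clinic adjustment.** With about four clinics and 13 events, the prescribed random effect is estimated as about zero in roughly half of runs at a true logit SD of 0.5. If clinic mix differs between attenders and controls, the analysis under-adjusts. Under the assumed scenarios the null bias was about +0.3 to +0.55 log-odds, an odds ratio of exp(0.34) = 1.4 to exp(0.55) = 1.7 where the truth is 1. False positives were 6.6% to 13%, apart from the one scenario at 3.1%. If clinic mix is the same in both cohorts, little harm follows.
- **Linear mixed model.** At the planned rates its interval for the difference is clearly too narrow (coverage about 88%). This needs no assumption about clinics. The test is not inflated under equal rates (2.4% at 2%, 5.0% at 10%), so the interval is affected and not the type I error.
- **Intervals for proportions.** The omission of the binomial is a minor fault at the planned rates.

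**What to change.** For the binary primary outcome:

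1. Replace the random clinic effect by clinic as a stratum or fixed effect: a clinic-stratified exact or Cochran-Mantel-Haenszel analysis, or Firth logistic regression with clinic indicators and few further covariates. Firth still gives a finite estimate when controls have no events.
2. Remove linear mixed modelling from the options for comparing the proportions and for adjusting them.
3. Use Wilson or exact binomial 95% CIs for proportions.
4. Keep Poisson and negative binomial models for counts; use Poisson for a binary outcome only with robust variance.

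The change is to wording only, and the methods are available in the software the plan names. The price is fewer covariates in the adjusted model and a slightly conservative test (about 2% to 4% rejection at a nominal 5% in most of the null scenarios above, 1% in one).

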#### Analysis sets

The analysis for the primary outcome will include all clients from catchment clinics who attend the PCMed Service and historical controls. A sensitivity analysis will consist of all eligible women attending catchment clinics from the commencement of the study period, regardless of whether they attended the PCMed Service, and historical controls.

#### Analysis of the primary outcome

##### Effectiveness of the PCMed Service intervention

The proportion of women who start RRMeds within 12 months of a catchment clinic consultation will be summarised preimplementation and postimplementation of the PCMed Service using descriptive statistics. Event proportions will be compared using a χ^2^, Fisher’s exact test or linear mixed modelling as indicated. Differences in the distribution of confounders between the historical and prospective cohorts will be managed using univariable and multivariable logistic, Poisson and/or negative binomial regression and/or linear mixed modelling as indicated.

### Analysis of secondary outcomes

#### Effectiveness of the PCMed Service

Descriptive statistics will be used to summarise the proportion of women (without contraindications^24^) who used RRMeds within 6 months of their PCMed Service consultation and the reason for non-use of RRMeds at 6 months after the initial consultation at PCMed Service, where a decision was made whether to take RRMeds.

#### Adoption of the PCMed Service

The proportion of women who attended each catchment clinic and who subsequently attended the PCMed Service within 6 months of a catchment clinic consultation will be summarised using descriptive statistics. Associations between participant characteristics and the likelihood of adoption will be analysed using logistic regression. This analysis will use the sensitivity analysis. Descriptive statistics will be used to summarise the reason(s) for declining a referral to the PCMed Service as an exploratory endpoint.

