### Aims

The overarching aim is to evaluate the effectiveness and process of implementing this new clinical service.

The primary aim is:

To determine whether the PCMed Service is associated with an increased use of RRMeds by women who attend catchment clinics, compared with use by similar women who attended catchment clinics before the implementation of the PCMed Service.

Secondary aims include:

To describe the adoption of the PCMed Service by women who attend catchment clinics. Specifically, the proportion of eligible women who attend the PCMed Service following a catchment clinic appointment where the PCMed Service is discussed.To determine the uptake of RRMeds for all clients who attend the PCMed Service and the associated characteristics.To explore the reasons for not taking up RRMeds and the associated characteristics.To explore the acceptability of the PCMed Service to clients.To explore the acceptability of the PCMed Service to clinicians.To determine the feasibility and fidelity of the PCMed Service intervention and any adaptations required.To evaluate the cost of delivering the PCMed Service from the perspective of the healthcare provider.

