### Recruitment to the PCMed Service and study

Prior to the commencement of the PCMed Service, clinicians working in the catchment clinics, including breast care nurses, were informed of the PCMed Service and its concurrent evaluation. Resources were developed and placed in the catchment clinics. These include a client brochure and a clinician fact sheet that describes the Service, eligibility criteria and the referral process.

Eligible women are actively recruited for the PCMed Service from catchment clinics by the nurse practitioner ([name]), who reviews the electronic medical records of women in advance of their catchment clinic appointment and identifies those who are potentially eligible for the PCMed Service. Clinicians seeing these women are reminded by [name] of the PCMed Service and asked to provide eligible women with a client brochure and to refer them to the PCMed Service if appropriate.

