### Outcome measures and data collection

#### Effectiveness of the PCMed Service intervention (primary aim)

The use of RRMeds by similar women before and after the implementation of the PCMed Service will be assessed 12 months after attendance at a catchment clinic. To determine the use of RRMeds prior to the implementation of the PCMed Service, a retrospective chart review is collecting data on consecutive eligible women (historical controls) who attended catchment clinics prior to the commencement of the PCMed Service. For women who attended familial cancer centre catchment clinics, the BOADICEA risk prediction model^35 36^ is routinely applied, and each individual’s risk is documented in their medical record. Other catchment clinics did not consistently apply risk prediction models. Therefore, the first author ([name]) applies one of the three prediction models at the time of data collection (with the choice of prediction model dependent on which is most appropriate based on the available data). First author ([name]) extracts the following data from the medical record for each woman: date of birth, indigenous status, country of birth, socioeconomic status, marital status, parity, education level, whether an interpreter was required, catchment clinic attended, type of clinician seen in the catchment clinic (eg, geneticist, medical oncologist), date of last catchment clinic consultation, whether RRMeds were discussed at that consultation and whether the client had commenced RRMeds within 12 months after the last consultation in the catchment clinic. Comparable data are being collected for the prospective group of women who attend the catchment clinics after commencement of the PCMed Service, regardless of whether they attend the new PCMed Service. For historical controls and those in the prospective cohort, if the first author, [name], is unable to find evidence of a discussion about RRMeds in the woman’s electronic medical record (clinic notes and correspondence), it is presumed that RRMeds were not commenced. It is noted that not all clinicians might routinely document everything discussed in a consultation. Therefore, the prescription history in the medical record is also reviewed. If a discussion about RRMeds is documented, or the prescription history indicates that a RRMed was prescribed, women are contacted to ascertain if RRMeds were commenced within 12 months of that consultation.

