#### Adoption of the PCMed Service

To what extent the PCMed Service intervention is adopted will be measured by the attendance of clients at the Service within 6 months following a documented discussion about the Service at the relevant catchment clinic.

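### Adoption is tied to a discussion of the Service in the aim and outcome measure, but the planned analysis drops that condition and names a set that literally includes historical controls

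*Protocol article*

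**What the plan says.** All references are to the protocol article, which describes adoption in several places.

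- **Aims, secondary aims:** "the proportion of eligible women who attend the PCMed Service following a catchment clinic appointment where the PCMed Service is discussed".
- **Outcome measures and data collection, Adoption of the PCMed Service:** "attendance of clients at the Service within 6 months following a documented discussion about the Service at the relevant catchment clinic".
- **Analysis of secondary outcomes, paragraph on adoption:** the quantity given a descriptive summary is "The proportion of women who attended each catchment clinic and who subsequently attended the PCMed Service within 6 months of a catchment clinic consultation". Logistic regression then relates participant characteristics to the likelihood of adoption, followed by the sentence "This analysis will use the sensitivity analysis".
- **Analysis sets:** "A sensitivity analysis will consist of all eligible women attending catchment clinics from the commencement of the study period, regardless of whether they attended". Attendance here means attendance at the Service, and the historical controls are also part of the set.

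Two other sections bear on whether these definitions select the same women. Under Recruitment to the PCMed Service and study, clinicians are reminded of the Service and "asked to provide eligible women with a client brochure and to refer them to the PCMed Service if appropriate". The section on the primary aim acknowledges, when dealing with discussions of medication, that "not all clinicians might routinely document everything discussed in a consultation".

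**The concern.** The outcome measure and the analysis differ in two respects: who is in the denominator, and when the 6 months begin. A woman with whom the Service was never raised has no starting point under the outcome measure. Under the analysis section she is in the denominator and counts as a non-adopter.

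The Discussion says the study will explore factors influencing adoption in order to understand barriers to engagement and improve uptake. A single proportion over all attendees cannot show whether a low value reflects clinicians not raising the Service or women not taking it up. The regression has the same difficulty: a characteristic that predicts being told of the Service can appear as one that predicts a woman's decision to attend.

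**Working it through.** The article states no adoption figure, target or sample size, so there is no planned number to reproduce. The check sets the definitions side by side and then works out what follows.

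**1. Definitions compared**

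| Place | Discussion required? | 6 months start at |
|---|---|---|
| Aims | Yes | No window given |
| Outcome measures | Yes, documented | The documented discussion |
| Analysis of secondary outcomes | No | A catchment clinic consultation |
| Analysis sets (sensitivity set) | No; historical controls included | Not applicable |

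**2. Effect on the proportion**

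Let f be the share of eligible prospective women with a discussion, r1 the attendance rate among them, and r0 the rate among the rest. None of the three is given in the article.

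- Aim and outcome measure: r1.
- Analysis section, prospective women only: P = f·r1 + (1 − f)·r0.
- Shortfall: r1 − P = (1 − f)(r1 − r0).

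The shortfall is positive only if f < 1 and r0 < r1. With assumed values:

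| f | r1 | r0 | P |
|---|---|---|---|
| 50% | 50% | 0% | 25% |
| 50% | 50% | 5% | 27.5% |
| 75% | 30% | 0% | 22.5% |
| 75% | 30% | 5% | 23.75% |
| 100% | any | – | r1 |

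**3. Effect on the logistic model**

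Take two groups of women with the same r1 = 50% and r0 = 0%, but f = 75% in one and 50% in the other. Among women with a discussion the odds ratio for attendance is 1. Over all attendees the proportions are 0.75 × 0.50 = 37.5% and 0.50 × 0.50 = 25%. The odds ratio is (0.375/0.625)/(0.25/0.75) = 0.600/0.333 = 1.8, produced entirely by who was told. The clinic random effect described under Inferential statistics could absorb differences between clinics in how often the Service is raised. It would not absorb selective raising within a clinic.

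**4. Historical controls**

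If A of N prospective women attend, the sensitivity set taken literally gives A/(N + 100), since 100 controls are planned. None of those 100 could contribute to A.

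**5. Start of the window**

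For a woman seen more than once, the consultation that starts the clock need not be the one at which the Service was raised. The article does not say which consultation counts, so the direction of this effect is undetermined.

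**6. A limit on the narrower definition**

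Suppose every attender's discussion is documented, but only a share g of discussions with non-attenders. The estimate is then r1/(r1 + (1 − r1)·g). With r1 = 30% and an assumed g = 75%, it is 0.30/(0.30 + 0.525) = 36.4%, so under-documentation pushes this version upwards.

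**The case against.** The strongest reply is that this is loose wording in a condensed article. The Abstract describes adoption simply as the proportion of women who attend, with no mention of a discussion. The aim could be read with all eligible women as the denominator and the discussion qualifying the event. The outcome measure gives an event and a window but no explicit denominator. The sentence naming the sensitivity set may refer only to the regression. The nurse practitioner screens records and prompts clinicians before appointments, so coverage may be high, and with full coverage the proportions over prospective women agree apart from any difference in time origin.

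Part of this stands: the documents do not establish that the all-attendee proportion is illegitimate, or how many eligible women go without a discussion. But the outcome measure's clock cannot start without a documented discussion, and the analysis section names a different starting event and population. That is a conflict rather than an omission. Confining the sensitivity set to the regression does not help, because the sentence defining the proportion lacks the condition too, and the regression is where the mixing does most harm.

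A reader might infer that the implementation decision would be reversed. That goes too far. Adoption is a descriptive secondary outcome with no threshold, reasons for declining a referral are summarised separately, and clinician interviews cover the referral process.

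**Conclusion.** The inconsistency is real and affects a named secondary aim. Followed as written, the analysis estimates a different quantity from the one in the aim and outcome measure, and its regression does not isolate women's uptake of the Service. The proportion will be lower than intended if some eligible women have no discussion and those women attend less often. Both conditions are plausible, since raising the Service is left to the clinician, but neither is documented.

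The size cannot be calculated from the article. A reader might be tempted to use the recruitment counts under Sample size considerations, taking 35/278 = 12.6% as adoption under the analysis section and scaling it up for assumed discussion rates. The documents do not support this. The 35 are described only as eligible for the primary analysis, not as the attenders. The 278 may include women referred from outside the catchment clinics. The counts are interim, so some women may not have completed 6 months. Nor can it be said without qualification that the reported figure will be too low, because that depends on the unknown discussion rate.

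**What to change.** In the adoption paragraph under Analysis of secondary outcomes:

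1. Restrict the analysis to eligible women in the prospective cohort and state that historical controls are excluded.
2. Define adoption as attendance within 6 months of a documented discussion of the Service, among eligible women with such a discussion, and fit the adoption regression in that set.
3. Report reach separately: the share of eligible attendees with a documented discussion.
4. Keep attendance among all eligible prospective attendees as a third figure, labelled as such.

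The change is mainly one of wording, because the outcome measure already requires the discussion to be identified. The data items listed for the primary aim mention discussion of medication rather than of the Service, so the team should confirm that the latter is recorded for every eligible attendee.

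There are two costs. The denominator is smaller, so the confidence interval is wider. Adoption may also be overestimated if discussions with women who decline are recorded less often than those with women who attend, which is why the all-eligible figure should be shown alongside.
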